### Recruitment procedure

As part of standard antenatal care, two midwives responsible for coordinating antenatal mental health care at the Department of Obstetrics, Rigshospitalet, Copenhagen University Hospital, will contact all pregnant women with current or previous mental health problems by telephone. Women considered eligible for the EWE Study will be made aware of the study and their opportunity to participate. Women showing interest in participating in the study and who give verbal consent to receive written information will be sent an invitation with a detailed description of the study. Approximately 2 weeks after the information has been sent, a research midwife will contact the women by telephone to ensure the invitation has been received and to answer preliminary questions. Women who are interested in further information about the study will be invited to a face-to-face meeting with a research midwife at the Department of Obstetrics, Rigshospitalet, Copenhagen University Hospital. At this meeting, the women will receive more information about the study and will have the opportunity to ask questions. If the women decide to participate, the baseline questionnaire will be completed, hand grip strength test will be measured by a North Coast Hydraulic Hand Dynamometer (North Coast Medical, Gilroy, CA, USA) [26], and randomization will be carried out (*see* Fig. 1). The participants will be randomly assigned to either the intervention or the control group in a ratio of 1:1.

**Fig. 1 Fig1:**
[figure not shown]
The expected flow diagram of progress through the study

### Randomization

Simple randomization will be performed on the Internet by a project midwife. The randomization code will be generated by a specially designed computer program (Lucidity Software, Melbourne, Australia) in cooperation with the Department of Clinical Medicine, The University of Aarhus, Aarhus C, Denmark.

### Blinding

Because of the nature of the intervention in this RCT, double-blinding is not possible. The statistician performing the statistical analyses will be blinded to intervention or the control group allocation.

### Sample size estimation

The sample size estimation is based on the primary outcome—psychological well-being—measured by the WHO (Five) Well-being Index (WHO-5) [27]. A sample size calculation was carried out to detect a 10-point higher score on the WHO-5 at 29–34 weeks of gestation in the intervention group compared with the control group. A 10-point difference in the WHO-5 score between the intervention and control groups is considered clinically significant [28, 29], and an SD of 16 was used. This SD is based on a previous assessment of the WHO-5 score in a population of 3970 pregnant women with and without mental disorders measured at 10–12 weeks of gestation in the total population of pregnant women at Rigshospitalet, Copenhagen University Hospital. This SD value (16 points) was used in the sample size calculation because we did not have an SD in the WHO-5 score measured at 29–34 weeks at our disposal. We expect 50% of the participants to follow the program for at least 75% of the sessions (high participation, 19–24 sessions), whereas 35% will participate in 50% to 75% of the sessions (moderate participation, 12–18 sessions) and 15% will engage in less than half of the sessions (low participation). We expect high participation in the exercise intervention to lead to an increase of 10 points in the WHO-5 score, moderate participation to lead to an increase of 7 points, and low participation to lead to an increase of 2 points compared with the control group. This will lead to the intervention group’s having an average value 7.75 points (0.50 × 10 + 0.35 × 7 + 0.15 × 2) higher than that of the control group at 29–34 weeks of gestation. With a power of 90% and a two-sided significance level of 5%, a difference in well-being level of 7.75 points (SD 16) in the two groups at 29–34 weeks of gestation can be detected by a two-sample *t* test with 91 patients in each group.

We expect that it will be necessary to include a total of 300 pregnant women because we anticipate that 13% (20 women) in each group will drop out as a result of discomfort or complications related to pregnancy and that 39 women (30%) of the remaining 131 participants in each group will not answer the questionnaire at 29–34 weeks of gestation, leaving 91 participants in each group.

### Intervention group

The intervention group will be offered an exercise program delivered to groups of 10–12 pregnant women at the hospital twice weekly for 12 weeks from baseline (17–22 weeks of gestation) in addition to standard antenatal care as described for the control group. The exercise program (*see* Table 1) will be carried out in accordance with the Danish national recommendations for exercise during pregnancy [30] and developed by physiotherapists from Rigshospitalet, Copenhagen University Hospital, who will also supervise the exercise sessions. The duration of a session will be 70 minutes, and one session will consist of a 10-minute warm-up (Borg scale 7–10); 20 minutes of endurance training on exercise bikes, treadmills, or cross-trainers (Borg scale 11–15); 25 minutes of strength training (back, abdomen, thighs, arms, and pelvic floor); and 15 minutes of stretching and relaxation (Borg scale 6) [31, 32].

**Table 1 Tab1:** Intervention group exercise program

Duration	Intervention	Description of exercise	Load
10 minutes	Warm-up Up to each teacher Has to include: • Light cardiovascular exercise • Mobilization of shoulder/back/pelvis	Examples: Neck stretching: standing in a circle, perform shoulder rotations and elevations Exercise of low intensity Walking in a circle: forward, backward, and sideways Shoulder/spine/pelvic mobility 1. Arm swings (one arm + both arms) 2. Arm swings in a kayak-paddling motion 3. Lateral flexions 4. Pelvic tilts (anterior, posterior, bilateral, figure eights) 5. On all fours, flexion/extension of the spine to find the neutral position	Borg Scale 7–10
20 minutes	Endurance training	Exercise bikes, treadmills, or cross-trainers	Borg Scale 11–15
25 minutes	Strength training Pelvic floor	1. On all fours: elevation of the extremities to engage the back and hamstrings; diagonal lift, 3 × 10 repetitions followed by a 10-second isometric hold; there is a short break after each isometric hold 2. Supine position: upper extremity flexion/extension to strengthen the upper arms and pectoral muscles; 3 × 10 repetitions; 60-second break after each of the three sets 3. Squats: strengthening of the thighs and gluteal muscles; 3 × 12 repetitions; 60-second break after each of the three sets Supine position (or side-lying position if preferred) 1. Short muscle squeeze × 10 2. Squeeze held for 6–8 seconds × 20 with a 6- to 8-second break between each squeeze 3. Squeeze held for 30 seconds × 2 with a 15-second break between each squeeze	60–70% of one-repetition maximum endurance
15 minutes	Stretching and relaxation Up to each teacher Has to include: • Breathing exercises • Relaxation • Stretching	Example: Relaxation compact disc or verbal guiding with emphasis on breathing; approximately 5 minutes Stretching of the big muscle groups: • Pectoralis major • Gluteus maximus • Quadriceps • Triceps surae	Borg Scale 6

The participating women’s general practitioners will be informed about the intervention and will be encouraged to support them to continue participating in the exercise program. Furthermore, a weekly supportive email will be sent to the participants to increase compliance, and the participants in both groups will be informed that they can contact the research group if they have questions related to the trial.

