The Effect of Group Exercise on Mental Wellbeing among Pregnant Women at Risk of Perinatal Depression trial (EWE Study) is a large randomized controlled trial (RCT) using supervised exercise in groups twice weekly for 12 weeks as an intervention for pregnant women at risk of depression and anxiety. The intervention period is 12 weeks because a major meta-analysis based on 49 studies of exercise and depression found that a training period of 10–16 weeks had the best effect on symptoms of depression [19]. Supervised exercise in groups was chosen because pregnant women experience a sense of security when they exercise together in professionally led sessions where the professional can monitor the extent of the physical exercise and provide guidance [21].

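### The 90% power figure makes no allowance for within-group correlation, although one arm is treated in exercise groups of 10–12

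*Protocol article*

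**What the plan says.** Allocation is individual. Under Randomization, "Simple randomization will be performed on the Internet by a project midwife", and under Recruitment procedure women are "randomly assigned to either the intervention or the control group in a ratio of 1:1".

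Delivery in the intervention arm is collective. Under Intervention group, women are offered an "exercise program delivered to groups of 10–12 pregnant women at the hospital twice weekly for 12 weeks", led by physiotherapists. Table 1 leaves the choice of warm-up and of stretching and relaxation to the instructor, within required components, and fixes the endurance and strength parts. The Background makes the group setting part of the rationale: "Supervised exercise in groups was chosen because pregnant women experience a sense of security when they exercise together". The Control group section describes standard antenatal care without exercise groups.

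Under Sample size estimation the target is 90% power at a two-sided 5% level for a WHO-5 difference of 7.75 points, SD 16, at 29–34 weeks. The article states that this "can be detected by a two-sample *t* test with 91 patients in each group". The increase to 300 randomized covers dropout and questionnaire nonresponse only. No ICC, design effect or group term appears in the article.

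Data analysis specifies intention to treat, multiple imputation and a per-protocol analysis. It names t tests for baseline comparisons but no test or model for the primary outcome.

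**The concern.** Women who train together share an instructor and each other's company twice a week for 12 weeks. By the article's own reasoning the group is part of how the treatment works, so intervention-arm outcomes may be correlated within groups while control outcomes are not. This is a partially nested design: individually randomized, clustered in one arm.

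The sample size treats all 182 analysed women as independent. If responses are correlated within groups, the intervention-arm mean is less precise than assumed. An analysis that recognizes the groups then has less than 90% power. An analysis that ignores them understates the standard error. A later analysis plan can choose between these, but it cannot make a 90% figure derived under independence correct.

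**Working it through.** **Inputs from the article:** difference 7.75, SD 16, two-sided 5%, 91 analysable of 150 randomized per arm, groups of 10–12 in the intervention arm only, recruitment from July 2016 to December 2018.

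**Assumed, because the article gives no value:** ICC 0.01 to 0.10; total SD of 16 in both arms; discrete groups with responders spread evenly.

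**1. The plan's own figure.** The exact t-test power for 7.75/16 is 0.898 at 90 per arm and 0.901 at 91. So 91 reproduces as the smallest n that reaches 90% under independence, and it contains no allowance for clustering.

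**2. Responders per group.** Taking the mid-size of 11, 11 × 91/150 ≈ 6.7 (range 6.1 to 7.3 for groups of 10 to 12).

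**3. Design effect, intervention arm only.** DE = 1 + (6.7 − 1) × ICC. The standard error of the difference is SE = 16 × √((1 + DE)/91). With DE = 1 this is 2.372. Inflating both arms would overstate the loss.

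**4. Power of an analysis that uses the correct SE.** Power = Φ(7.75/SE − 1.96). Example at ICC 0.05: DE = 1.285, SE = 16 × √(2.285/91) = 2.535, 7.75/2.535 = 3.057, Φ(1.097) = 0.864.

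**5. Type I error if the plain t test were the analysis and groups truly differ.** This is 2 × [1 − Φ(1.973 × √(2/(1 + DE)))], where 1.973 is the t critical value on 180 degrees of freedom. At ICC 0.05: 1.973 × √(2/2.285) = 1.846, giving 6.5%.

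**6. Few groups.** A simulation (40,000 runs per setting, 13 groups of 7 against 91 controls) tested group means against individual controls with Satterthwaite degrees of freedom. It also recorded the rejection rate of the plain t test with no mean difference.

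| Assumed ICC | DE | SE | Power, normal approx. | Power, simulated group-level test | Type I, plain t test (formula) | Type I, plain t test (simulated) |
|---|---|---|---|---|---|---|
| 0.01 | 1.06 | 2.41 | 89.6% | 88% | 5.2% | 5.2% |
| 0.02 | 1.11 | 2.44 | 88.8% | 87% | 5.5% | 5.7% |
| 0.05 | 1.29 | 2.54 | 86.4% | 84% | 6.5% | 6.8% |
| 0.10 | 1.57 | 2.69 | 82.2% | 79% | 8.2% | 8.5% |

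The simulated group-level test held its error at 5.0% to 5.1% throughout.

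**7. Upper bound on group size.** If all 12 members of each group counted in the analysis, power by the same formula would be 82.5% at ICC 0.05 and 74.7% at ICC 0.10.

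**8. Are closed groups plausible?** 150 intervention women over 30 months is about 5 a month if accrual is even. Filling a closed group of 10–12 would take 10/5 = 2.0 to 12/5 = 2.4 months, or roughly 9 to 10 weeks. That is longer than the 17–22-week window in which women must start. Rolling entry with overlapping membership is therefore quite possible, and steps 3 to 6 are then approximations.

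**9. Can baseline adjustment make up the loss?** Adjustment with baseline–outcome correlation r multiplies the variance by about (1 − r²). Full recovery needs (1 + DE)/2 × (1 − r²) = 1, so r = √(1 − 2/(1 + DE)). This is √(1 − 2/2.285) = 0.35 at ICC 0.05 and √(1 − 2/2.57) = 0.47 at ICC 0.10. The article gives no such correlation.

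**The case against.** **No ICC is documented.** This stands. At 0.01 to 0.02 the loss is about 1 point or less by normal approximation, and it becomes material only from about 0.05. The instructor's free choice covers 25 of the 70 minutes, with required content, which limits one source of differences between groups. The size is therefore conditional on an assumption. It remains true that the 90% claim takes the ICC to be exactly zero, with nothing in hand.

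**Type I error.** A reader might infer that the trial's type I error exceeds 5%. The article does not support that. It names the t test for the sample size, not for the primary outcome, and an analysis plan that is not shown may account for groups. Moreover, with individual randomization, if exercise affects no woman then her exercise group cannot alter her score, and the t test keeps about 5%. Inflation requires a zero average effect together with real differences between groups.

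**Number of groups.** Dividing 150 by 10–12 suggests 13 to 15 closed groups. The article does not say that groups are closed, and the expected accrual fits that poorly. The figures should not be read to a tenth of a percent.

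**Blinding.** Group codes in one arm reveal allocation to the statistician, who is to be blinded. This is a real cost of the remedy, but it can be managed by the order of work.

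**Conclusion.** The point holds for the power statement. One arm is treated in groups, the 90% assumes independence, and 91 per arm leaves no reserve. Over an assumed ICC of 0.01 to 0.10, power at 91 per arm is about 90% down to 82% by normal approximation, or about 88% down to 79% by the group-level test. This rests on about 6.7 responders per group, an SD of 16 in both arms and discrete groups.

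A type I error of about 5.2% to 8.2% would follow only if the plain t test were the analysis and groups truly differed; it is a risk to close off, not an established defect. It is also tempting to say that baseline adjustment restores the lost power. It may offset part of the loss, but full recovery at ICC 0.05 to 0.10 needs correlations of 0.35 to 0.47, which are unsupported here. The matter is moderate in size and should be corrected.

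**What to change.** - Record each intervention woman's exercise group and instructor as she starts, or her start cohort if entry is rolling. Membership may be hard to reconstruct later.
- Analyse WHO-5 at 29–34 weeks with a partially nested mixed model: a random group effect in the intervention arm only, each control standing alone, and small-sample degrees of freedom (Satterthwaite or Kenward–Roger). With overlapping membership, use start cohort or multiple-membership weights.
- Reflect group in the multiple imputation, so that the imputed values do not dilute the correlation.
- Fix the analysis scripts before group codes reach the blinded statistician.
- Replace the 90% claim with power over a stated ICC range and responding group size, and say whether groups are closed or rolling. If baseline WHO-5 adjustment is cited as an offset, state the correlation assumed.

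The cost is a little extra data recording, some analysis-plan wording, slightly wider intervals if groups differ, and a lower stated power. No further enrolment is proposed.

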### Control group

Women in the intervention group as well as those in the control group will be offered the standard antenatal care for pregnant women with a current or previous history of depression and/or anxiety. Standard care for this group covers a coordinated program including more frequent and lengthier prenatal consultations with specialized midwives and obstetricians who have particular experience with pregnancy and mental disorders. If the pregnant women are treated with antidepressants, additional ultrasound scans to assess fetal growth will be recommended. The specialized midwife coordinates the teamwork with obstetricians, psychiatrists, psychologists, social workers, and nurses.

### Outcome measures

Data will be obtained at baseline and four times during the study period: at 17–22 weeks of gestation (T1), at 29–34 weeks of gestation (T2), 2 weeks after delivery (T3), and 2 months after delivery (T4). The SPIRIT figure (*see* Fig. 2) provides an overview of the outcome measures used in the trial and their time points. The participants will fill out the first electronic questionnaire at the face-to-face meeting where randomization takes place, and they will receive a link to the two following questionnaires (T2, T4) by email. Prior to the data collection, an email is sent to the participants reminding them of the upcoming data collection.

**Fig. 2 Fig2:**
[figure not shown]
Consolidated Standards of Reporting Trials (CONSORT) showing time points of enrollment, intervention, and outcome measures

#### Primary outcome

Psychological well-being, the primary outcome, will be measured by the WHO-5 score. The WHO-5 is a short generic rating scale measuring general subjective current (the last 2 weeks) psychological well-being [27]. The questionnaire has five items and covers positive mood (feeling in good spirits), vitality (being active and waking up feeling refreshed and well-rested), and being interested in things [33]. It contains five positively phrased items; each item is scored on a Likert scale (0 = none of the time and 5 = all of the time). The raw score ranges from 0 (absence of well-being) to 25 (maximal well-being) and is multiplied by a factor of 4 to give a scale ranging from 0 to 100, where a score of 0 is the lowest possible well-being and a score of 100 is the highest possible well-being [27]. WHO-5 has high clinimetric validity, and it can be used as an outcome measure in clinical trials in addition to a clinical screening tool for depression [27].

#### Secondary outcomes

Five secondary outcomes will be measured:
*Symptoms of depression*, defined as a cutoff score ≥13 and a cutoff score ≥10 measured by the Edinburgh Postnatal Depression Scale (EPDS). EPDS is a self-reported questionnaire measuring depression and consisting of 10 items scored on a 4-point Likert scale (0–3). The scale addresses the intensity of common depressive symptoms within the previous 7 days, where 0 indicates absence of depressed mood and 3 indicates the worst mood. The lowest score is 0, and the highest score is 30. According to some literature, a cutoff score ≥13 indicates an increased likelihood of clinical depression [34, 35], whereas other studies suggest a cutoff score ≥10 to minimize the risk of failed detection of cases [35]. To meet the findings in previous studies, we will use two cutoff scores, ≥13 and ≥10, in our statistical analysis. The EPDS has been validated for the detection of antenatal and postpartum depression [34–36] and has previously been translated into Danish and then back-translated to check that the questions elicited the intended information [37].
*Functional ability*, measured by the 12-item General Health Questionnaire (GHQ-12). The GHQ-12 is used to measure psychological well-being in adults over the previous 2 weeks [38]. The GHQ-12 screens for symptoms common to any nonpsychotic disorders and is focused on two areas: the inability to carry out normal functions and the appearance of new and distressing psychological phenomena [38]. The GHQ-12 contains 12 items, and the total score of the GHQ-12 varies from 0 to 36 using a 4-point Likert scale (0–3) [39].
*Clinical symptoms of anxiety*, measured by the State-Trait Anxiety Inventory (STAI). The STAI has previously been used for pregnant women [40]. It consists of 40 items, but only the state scale of the inventory will be used in this study, because the state scale measures symptoms of anxiety as anxiety is defined according to DSM-5 [41]. The 20 items concerning state anxiety are scored on a 4-point Likert scale and indicate how well the participant is feeling today (1 = not at all, 2 = somewhat, 3 = moderately so, and 4 = very much so). The total score for state anxiety ranges from 20 to 80. This inventory has been reported to have a high degree of internal consistency and validity [42]. We have chosen to cite the original version of the STAI because this is recommended by leading Danish experts in the field.
*Sleep quality and sleep disturbances*, measured by the Pittsburgh Sleep Quality Index (PSQI). The PSQI is a subjective scale measuring sleep quality and sleep disturbances over a 1-month period [43]. The scale addresses quantitative aspects of sleep, such as sleep latency and sleep duration, as well as more subjective aspects, such as restfulness of sleep [43]. Overall sleep quality is measured by means of 19 questions, and the total score is based on 7 “component” scores, each of which has a range of 0–3 points. A score of 0 indicates no difficulty, whereas a score of 3 indicates severe difficulty. The sum of the component scores results in a “global” score ranging from 0 to 21 points, where 21 indicates severe sleep problems. The PSQI has been found to be useful in pregnancy research, and good internal consistency and construct validity have been reported [44].
*Pregnancy and delivery outcomes*, comprising sick leave (measured in days), hospitalization (measured in number of hospital admissions and days), labor onset (spontaneous or induced), use of epidural anesthesia during delivery (yes or no), duration of labor (measured in hours), mode of delivery (percentage of participants with spontaneous delivery, vacuum extraction, or cesarean section), birthweight (measured in kilograms), and birth length (measured in centimeters). This information will be obtained from patient records.

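### Symptoms of depression, the first-listed secondary outcome, is defined only by two cutoffs of the 0–30 EPDS score, with no comparison of the score itself

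*Protocol article*

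**What the plan says.** In the protocol article, the section on secondary outcomes opens with "Five secondary outcomes will be measured" and lists symptoms of depression first. That outcome is "defined as a cutoff score ≥13 and a cutoff score ≥10" on the EPDS. The same paragraph says that the scale addresses the intensity of depressive symptoms over the previous 7 days, and that "The lowest score is 0, and the highest score is 30".

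The reason given for the cutoffs is the earlier literature: some of it links ≥13 to a raised likelihood of clinical depression, and other studies prefer ≥10 so that fewer cases are missed. The paragraph concludes: "To meet the findings in previous studies, we will use two cutoff scores, ≥13 and ≥10, in our statistical analysis".

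The other scales are described by their scores, without cutoffs. For the STAI, for example, "The total score for state anxiety ranges from 20 to 80". GHQ-12 is given a 0–36 total and PSQI a 0–21 global score. The primary outcome, WHO-5, is a 0–100 score, and the sample size section compares it between arms with a two-sample t test.

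No EPDS mean, SD, expected proportion above a cutoff, treatment effect or power is stated.

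**The concern.** The outcome's name and the description of the scale both refer to the severity of symptoms, but the definition records only whether a woman lies above or below a line. The reasons given for the two lines concern case detection. Case detection is a reason to screen with a cutoff, and it does not show that a cutoff is a good measure of a difference between randomised groups.

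A cutoff treats all women on the same side of it as equal. A change that does not cross 10 or 13 contributes nothing, however large it is. The protocol recruits women with current or past illness, so it is reasonable to expect a spread of scores on both sides, and movement within either side is lost.

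What is at stake is the precision of one secondary result. A real shift in symptoms could be reported as an inconclusive difference in proportions when the collected data could have shown it.

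**Working it through.** **Inputs from the protocol article (sample size section).** Difference in WHO-5 7.75 points, SD 16, two-sided 5% level, power 90%, 91 women per arm.

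**Inputs that must be assumed.** The proportion p of controls above an EPDS cutoff, the effect on EPDS, and a normal score shifted by treatment.

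**Step 1: reproduce the plan's own figure.** The standardised effect is d = 7.75/16 = 0.484. The normal approximation gives n = 2(1.960 + 1.282)²/0.484² ≈ 89.6, so 90 per arm. The exact t-test solution is 90.5, so 91, as stated. Power with 91 per arm is Φ(0.484 × √(91/2) − 1.96) = 0.904. The planned figure is confirmed, and it concerns WHO-5 only.

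**Step 2: information kept by a cutoff.** For a normal score cut so that a proportion p lies above the cutoff z, the information kept relative to the score is φ(z)²/[p(1 − p)].

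- p = 10%: 0.1755²/0.09 = 0.342, loss 66%
- p = 20%: 0.2800²/0.16 = 0.490, loss 51%
- p = 30%: 0.3477²/0.21 = 0.576, loss 42%
- p = 50%: 0.3989²/0.25 = 0.637, loss 36%, the smallest loss possible

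At p = 6.5% the loss is 74%. That value is the lower end of the range for antenatal depression quoted in the Background. It is not an EPDS figure and serves only to mark the far end of the range.

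**Step 3: power, if the EPDS effect were also 0.484 SD with 91 per arm.** The proportion in the intervention arm is p₂ = 1 − Φ(z + 0.484). Power is Φ{(p − p₂ − 1.96·SE₀)/SE₁}, with SE₀ pooled under the null and SE₁ unpooled.

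- p = 10%: p₂ = 3.9%, power 37%
- p = 20%: p₂ = 9.2%; (0.1076 − 1.96 × 0.0524)/0.0518 ≈ 0.095, power 54%
- p = 30%: p₂ = 15.7%, power 64%
- p = 50%: p₂ = 31.4%, power 73%

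The score itself has about 90% power under the same assumption. For 90% power the score needs 90 women per arm by the same normal approximation. The cutoff needs 359, 225, 178 and 145 per arm at the four values of p.

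**Step 4: a smaller effect.** At 0.30 SD with 91 per arm, power is 53% for the score. For a cutoff it is 19%, 27%, 31% and 36% at the same four values of p. The ordering does not depend on borrowing the WHO-5 effect.

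**The case against.** The strongest reply is that this is a condensed article. The abstract lists the outcome simply as symptoms of depression by EPDS, the data analysis section describes no specific analysis for any secondary outcome, and a statistical analysis plan may add a total-score comparison. That is fair as far as it goes: the article does not rule out such an analysis. It does, however, state a definition, and that definition is binary only, so an analysis plan that follows it inherits the loss.

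The cutoffs are also prespecified and justified by comparability with earlier studies. A cutoff is not blind to women who start below it, because preventing a rise above it counts. Both arguments stand, and they are good reasons to keep the proportions. Neither is a reason to leave out the score.

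Some stronger readings are tempting and should be resisted:

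- **That about half the information is lost, or that the outcome has poor power, as plain fact.** Both depend on a proportion above the cutoff that the article does not give, and the power figures also need an effect on EPDS that it does not give. The sample size rests on WHO-5 alone, and no power is promised for EPDS.
- **That most women will lie below both cutoffs.** The eligibility criteria also admit women who are currently ill or taking antidepressants in pregnancy, and no EPDS distribution is given.
- **That this is the leading secondary outcome.** It is listed first of five, and none is called key.
- **That two unranked cutoffs inflate false claims.** If each were tested at 5% with no order, the chance of at least one false positive would be about 8.3–8.8% over the pairs of proportions tried, against 9.75% for independent tests. The cutoffs are nested and declared in advance, and an order between them may sit in a plan not shown. Nothing in the text favours one over the other.

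**Conclusion.** The point holds in a limited form. The stated definition reduces a 0–30 score to two yes/no results and names no comparison of the score, unlike the trial's other scales. Under a normal shift the cost is never below 36% of the information, and it reaches 74% over the range examined. A bounded score need not be normal, so these figures are a guide to size rather than a prediction for this trial. The power figures rest further on an EPDS effect equal to that assumed for WHO-5.

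The primary outcome, its analysis and the sample size of 300 are not affected. This is a cheap improvement to one secondary outcome and does not threaten the trial's main conclusion.

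**What to change.** State that symptoms of depression will be analysed as the between-group difference in EPDS total score at 29–34 weeks of gestation (T2), adjusted for baseline EPDS. Apply the same analysis at any later time point where EPDS is collected; the figure listing outcomes by time point is not shown, so this should be checked against it. Keep the proportions at ≥13 and at ≥10 as prespecified supportive results, which preserves comparability with earlier studies.

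No new data are needed, because the total score is already available from the items. The costs are a dated amendment to a published secondary-outcome definition while recruitment is under way, and a headline result that is less directly readable as case status than a proportion. Reporting the two proportions beside the mean difference offsets the second cost.
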